### 4.3. Statistical Methods

For all analyses, the IBM SPSS Statistics software (Version 28.0.0.0) (IBM Corporation, Armonk, NY, USA) [113] as well as R (Version 4.0.5) [114] and RStudio (Version 1.4.1106) [115] will be used. All primary and secondary outcomes will be assessed on a metric scale level at all measurement time points. Therefore, linear mixed models (LMMs) will be used for statistical analyses of all outcomes. In the repeated measured data, the time points will be nested within cases, so the cases will be the cluster variable. The time points will enter the model as a continuous variable from baseline (0) to the end of the study (3). Random effects for intercept will be estimated. Degrees of freedom will be calculated with Satterthwaite’s method implemented in a specific R package (lmerTest). The basic model will consist of a cross-level interaction and random effects for intercept and slopes.

Level 1:

$Outcome=\beta_{0j}+\beta_{1j}*time+\beta_{nj}*X_{nj}+r_{ij}$

Level 2:

$\beta_{0j}=\gamma_{00}+\gamma_{01}*group+\gamma_{0n}*Z_{0n}+u_{0j}$

$\beta_{1j}=\gamma_{10}+\gamma_{11}*group$ $+u_{1j}$

The cross-level interaction will be between time and the dichotomous group variable (intervention vs. control group). The fixed effect $\gamma_{10}$ will represent the average change over time, while the cross-level interaction $\gamma_{11}$ will represent the difference in change between both study groups. Possible covariates or confounding variables, such as age and gender, can enter the model at the placeholder $X_{nj}$ on level 1 or $Z_{0n}\;$ on level 2.

To analyze short- and medium-term effects, the metric scale time point variable will be changed to a factor variable. Pairwise comparisons will be used with correction for multiple testing to estimate differences between each measurement time point. We will test group differences on time points t1, t2, and t3 as between-group contrast. Within each group, we will compare baseline with program completion (t0 vs. t1) and baseline with follow-up (t0 vs. t2). Additionally, we will contrast program completion with follow-up (t1 vs. t2) and change between follow-up and the end of the study (t2 vs. t3). Moreover, there is no need to account for multiple testing for the two primary outcomes as the two clinical trials (F_clin_, W_clin_) are considered as two independent trials.

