According to the intention-to-treat (ITT) principle, all randomized cases will be included. In addition, only cases that have followed the per-protocol (PP) principle will be analyzed. While for ITT analysis, missing values will be imputed, in PP (complete case) analysis, only study participants with no missing values for the corresponding outcome will be analyzed. The ITT and PP analysis will be compared. An assessment of completed measurement time points will be used to test whether study participants who have completed all medical examinations differ in the corresponding outcome. Multiple imputation will be used to impute missing data in the ITT analysis. Influx and outflux statistics will be applied to identify factors that will serve as auxiliary variables for the imputation model. Sensitivity analysis will be performed to compare imputed with not imputed data.

The usage behavior data will be analyzed between the intervention and control group and within the intervention group. The analysis between the study groups will be done descriptively. For the analysis within the intervention group, the outlined model will be modified. Therefore, the group variable will be omitted, and a variable that codes usage behavior will replace the group variable in the model on level 2.

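### As the model is written, age and gender can only shift the outcome level: with complete or imputed data they leave the group-by-time effect unchanged, and in the usage analysis they remove no confounding of change

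*Protocol article*

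**What the plan says.** Section 4.3 (Statistical Methods) of the protocol article writes out a two-level linear mixed model. Time is the visit number, 0 to 3, and "The basic model will consist of a cross-level interaction and random effects for intercept and slopes".

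- **Slope equation:** "\beta_{1j}=\gamma_{10}+\gamma_{11}*group" plus a random slope u₁ⱼ. It has no covariate term.
- **Intercept equation:** group, the person-level placeholder Z₀ₙ and a random intercept.
- **Level 1 equation:** intercept, slope times time, a second placeholder Xₙⱼ with its own coefficient, and the residual.
- **Target:** γ₁₁, which "will represent the difference in change between both study groups".
- **Covariates:** "Possible covariates or confounding variables, such as age and gender, can enter the model at the placeholder" Xₙⱼ or Z₀ₙ.

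Time is also treated as a factor, with between-group contrasts at t1, t2 and t3. On missing data, "Multiple imputation will be used to impute missing data in the ITT analysis". The per-protocol analysis uses participants with no missing values for the outcome, and a sensitivity analysis compares imputed with non-imputed data.

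The same section then tests usage behaviour within the intervention group by putting a usage variable in the place of group on level 2. This serves the third hypothesis at the end of the Introduction, that more frequent and intensive use leads to better outcomes.

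**The concern.** The plan offers age and gender as possible confounders but gives them no place where they can act on the quantity it tests. Entry age and gender do not vary within a person. Without a covariate-by-time term they can explain who starts heavier or fitter, but not who changes more. A fit with them included returns the same difference in change as a fit without them, so describing it as adjusted would tell the reader nothing.

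Two things are at stake. In the randomised comparison, any precision available from predictors of change is not gained. In the usage analysis the exposure is chosen by the participant, so age and gender may be related both to usage and to change, and the adjustment as written cannot remove that.

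**Working it through.** **Inputs from the document (section 4.3):** the three model equations, time coded 0 to 3, imputed ITT data, complete-case PP data, and usage replacing group. The document gives no covariate effects, so every effect size below is an assumption. The sample size (section 2.6) contains no covariate term and is not affected. Its 79 and 64 per group reproduce from a two-sided two-sample t-test (78.49 and 63.77, rounded up).

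**Step 1: algebra.** The visit codes 0, 1, 2, 3 have mean 1.5 and squared deviations 2.25 + 0.25 + 0.25 + 2.25 = 5. A person's slope is (−1.5·y₀ − 0.5·y₁ + 0.5·y₂ + 1.5·y₃)/5. The weights sum to zero, so a constant added to all four visits drops out. With all four visits present, the estimate of γ₁₁ is the difference in mean slopes. Correlated random effects do not alter this: the slope regressors (1, group) are a subset of the intercept regressors (1, group, Z), and generalised least squares for the smaller equation then reduces to ordinary least squares. Placing age or gender at Xₙⱼ with a fixed coefficient gives the same level shift. The identity holds in each imputed data set, so it holds after pooling.

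**Step 2: numerical check.** Three simulated trials with 158 people (1:1), four visits and complete data. Assumed effects: age 0.8 on level and 0.3 on slope per SD; sex 0.5 on level and 0.2 on slope. Entries are γ₁₁ (SE) by REML.

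| Trial | Unadjusted | Age and sex as written | Age and sex also by time | Fall in SE |
|---|---|---|---|---|
| 1 | 0.13991 (0.11450) | 0.13991 (0.11450) | 0.19380 (0.10765) | 1 − 0.10765/0.11450 = 6.0% |
| 2 | 0.12759 (0.10724) | 0.12759 (0.10724) | 0.13408 (0.10483) | 1 − 0.10483/0.10724 = 2.2% |
| 3 | 0.04360 (0.11880) | 0.04360 (0.11880) | 0.06761 (0.11044) | 1 − 0.11044/0.11880 = 7.0% |

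Maximum likelihood and random-intercept-only fits also show no change between the first two columns.

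**Step 3: where the adjustment does act.**

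- *Group contrast at t3 (time as factor):* 0.317 (SE 0.473) becomes 0.443 (SE 0.410) in trial 1.
- *Non-imputed data with outcome-dependent dropout:* with 565 of 632 visits left (about 11% lost), 0.1774 (0.1138) becomes 0.1675 (0.1137). With 476 left (about 25% lost), 0.2013 (0.1338) becomes 0.2306 (0.1356). Over six such data sets the shifts ran from 0.001 to 0.029, and the SE rose in five.

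**Step 4: precision in the randomised comparison.** If the covariates explain a share R² of the variance in slopes, the SE falls by about 1 − √(1 − R²). For an assumed R² of 2% this is 1 − √0.98 = 1.0%; for 10% it is 1 − √0.90 = 5.1%; for 0 it is nil.

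**Step 5: usage analysis.** Assume a usage–age correlation of 0.4, an age effect on slope of −0.4 per SD, and no true usage effect. Leaving age out of the slope equation shifts the usage-by-time coefficient by 0.4 × (−0.4) = −0.16 per SD of usage. In 60 simulated complete data sets (75 people, four visits):

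| Usage model | Mean usage-by-time estimate | Rejections at nominal 5% |
|---|---|---|
| Unadjusted | −0.172 | 27% |
| Age as written | −0.172 (largest difference from unadjusted 5e-14) | 27% |
| Age and age-by-time | −0.005 | 3% |

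A second simulation, also with assumed effects and a true effect of zero, gave −0.15, −0.15 and 0.02.

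**The case against.** The best defence is that the text is permissive. It speaks of possible covariates that can enter a basic model; it does not promise an adjusted primary effect, and the choice of covariates is normally left to an analysis plan that is not shown here. The slot also has a use, since it sharpens the contrasts at t1 to t3. Both statements are true and they limit the weight of the point. They do not remove it, because the slope equation is printed in full without a covariate and the text names both places where confounders may go. This is a written specification, not missing detail.

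A reader might infer three stronger things that the document does not support.

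- *That chance imbalance biases the trial result.* Assuming 35% men and a 2 kg gender difference in change, imbalance at 75 per arm could move the effect by 1.96 × 2 × √(2 × 0.35 × 0.65/75) = 0.31 kg either way. Under 1:1 randomisation (section 3.1) the unadjusted difference in change is unbiased, and this movement is ordinary sampling error already inside the confidence interval.
- *That covariates enter only the intercept, or can never alter γ₁₁.* There is a level 1 slot as well, and the non-imputed sensitivity analysis does move.
- *That the plan conditions on consequences of the program.* A visit-varying participant variable at Xₙⱼ would change γ₁₁ (0.261 to 0.141 in one simulation), but the only covariates named are age and gender.

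**Conclusion.** The point holds in a limited form. For covariates constant within a person, the identity of adjusted and unadjusted γ₁₁ is exact in complete data, and so in the imputed ITT analysis and the complete-case PP analysis. It does not depend on any assumed effect size.

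For the randomised comparison the consequence is minor: no bias, and a loss of precision of roughly 1% to 7% of the SE across the assumptions tried, which could be nil because the document gives no covariate effects on change.

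The usage analysis is the stronger reason to act. There the adjustment as written leaves confounding of change by age or gender entirely in place. The shift of about −0.16 and the 27% false-positive rate follow from the assumed correlation and age effect; the real size is unknown. Correcting the model would deal only with the covariates included, so other reasons why some participants use the program more would remain.

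**What to change.** Add the same covariates to the slope equation: β₁ⱼ = γ₁₀ + γ₁₁·group + γ₁ₙ·Zₙ + u₁ⱼ. Keep them in the intercept equation, and include Z-by-time terms when time is a factor. Name the covariates in advance, restrict them to values recorded at or before t0, and centre them. Make the same change in the usage model, with usage in place of group. If no adjustment of change is intended in the randomised comparison, say so, and state that the covariates serve only the contrasts at t1 to t3.

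The cost is a line in the model specification and a few degrees of freedom: one more slope term per covariate with continuous time, one per follow-up visit with time as a factor. No new data are needed.

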### 2.6. Sample Size

The sample sizes of the clinical trials (F_clin_, W_clin_) were calculated with regard to the long-term effect (t0–t3) of the respective primary outcome (F_clin_: VO_2_max, W_clin_: body weight) using G*Power software (Version 3.1) (Heinrich-Heine-Universität Düsseldorf, Düsseldorf, Germany) [109]. Based on comparable studies [50,110,111], effect sizes of Cohen’s *d* = 0.45 (F_clin_) and *d* = 0.50 (W_clin_), as well as a significance level of 0.05 and a statistical power of 0.80 were assumed. For the fitness trial (F_clin_), this resulted in a required case number of *n* = 79 for both the intervention and control groups. For the weight loss trial (W_clin_), the required case number was *n* = 64 for both study groups. Allowing for an additional dropout rate of 15% in each trial, the total target sample size was found to be *n* = 186 (93 + 93) (F_clin_) and *n* = 150 (75 +75) (W_clin_). Due to limited resources, there are no plans to exceed these sample sizes. Details can be found in the study protocol of the online trials [71].

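### The protocol does not say whether the slope interaction or the t3 group contrast decides each trial, so the stated power of 0.80 is not secured

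*Protocol article*

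**What the plan says.** Section 2.6 (Sample Size) states that the sample sizes "were calculated with regard to the long-term effect (t0–t3) of the respective primary outcome", with d = 0.45 for the fitness trial and d = 0.50 for the weight trial, and that "a significance level of 0.05 and a statistical power of 0.80 were assumed". No adjustment of the 0.05 is mentioned. The results are 79 and 64 per group, raised to 93 and 75 per group for 15% dropout.

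Section 4.3 (Statistical Methods) describes these analyses of the same outcome:

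- A basic mixed model with time as a continuous variable coded 0 to 3. Its time-by-group interaction is the group difference in change. No correction is attached to it.
- A second model with time as a factor, introduced for short- and medium-term effects. The next sentence reads "Pairwise comparisons will be used with correction for multiple testing to estimate differences between each measurement time point". The sentences after it list group contrasts at t1, t2 and t3, and four contrasts between time points within each group.

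The correction method and the family are not given. The one explicit exemption, that "there is no need to account for multiple testing for the two primary outcomes", rests on the two trials being independent of each other. It does not address several tests of one primary outcome inside a trial. The hypothesis at the end of the Introduction names no time point and no model parameter.

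**The concern.** The stated power belongs to one test: a two-group comparison of the t0–t3 effect at the full 0.05. The analysis section offers a slope over four visits, which is a different quantity, and a t3 contrast that may be tested at a smaller alpha. Until one of them is named, the reader cannot tell whether 0.80 applies. An analyst who sees the data can also choose which result to call the trial's answer.

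Two features sharpen this. Section 3.2 says the data analysts will not be blinded. Section 2.6 says the sample sizes will not be exceeded, so lost power cannot be recovered by recruiting.

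**Working it through.** **Inputs.** From section 2.6: d = 0.45 with 79 per arm, d = 0.50 with 64 per arm, alpha 0.05, power 0.80, dropout 15%. Sidedness is not stated. Two-sided is inferred, because one-sided 0.05 would need only about 62 and 50 per arm. The correction method, the family and the correlation between visits are not given, so they are assumptions below.

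**1. The plan's own figure.** Two-sample t-test, noncentrality d × √(n/2), 2n − 2 degrees of freedom.

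- Fitness: 0.45 × √39.5 = 2.828; power 0.803.
- Weight: 0.50 × √32 = 2.828; power 0.801.

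Both reproduce, and 79 and 64 are the smallest sizes that reach 0.80. Dropout: 79/0.85 = 92.9, stated as 93; 64/0.85 = 75.3, stated as 75. The stated sizes are therefore those of a two-group comparison at unadjusted two-sided 0.05.

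**2. If the corrected t3 contrast decides.** Bonferroni over three contrasts gives alpha = 0.05/3 = 0.0167.

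- Power at the planned completers: 0.658 (fitness) and 0.656 (weight).
- Completers per arm needed to restore 0.80: 105 and 86.
- With no dropout at all (93 and 75 per arm): about 0.74.
- Holm instead of Bonferroni, equal effects at t1, t2 and t3: simulated power at t3 is about 0.745 at correlation 0.5, 0.733 at 0.8 and 0.72 at 0.9.

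**3. If the slope decides, at full 0.05.** Assume compound symmetry with within-person residual variance τ². Take d as the group difference in t0–t3 change, e₃, divided by the SD of that change, √2·τ. With visits coded 0–3 the slope weights c are −1.5, −0.5, 0.5, 1.5, with sum of squares 5. The standardised slope effect is then d × (√2/√5) × Σ(c·e)/e₃ = d × 0.6325 × Σ(c·e)/e₃.

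| Effect at t0, t1, t2, t3 (t3 = 1) | Σ(c·e)/e₃ | Multiple of d | Power, both trials |
|---|---|---|---|
| Steady growth: 0, 1/3, 2/3, 1 | 1.667 | 1.054 | 0.84 |
| Plateau: 0, 1, 1, 1 | 1.500 | 0.949 | 0.76 |
| Fading: 0, 1.5, 1.25, 1 | 1.375 | 0.870 | 0.69 |
| Fading: 0, 2, 1.5, 1 | 1.250 | 0.791 | 0.60 |

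These use the same t-test calculation as step 1. A normal approximation raises each by less than 0.01, to about 0.85 in the first row and 0.61 in the last.

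**4. If either may count as success.** Simulated under no effect with compound symmetry: slope at |z| > 1.96, or any of the three between-group contrasts at |z| > 2.39 (two-sided 0.0167). The error rate is 8.9% at correlation 0.5 and 7.8% at 0.9. If the contrasts are taken as changes from baseline it is about 7.4%.

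**The case against.** The strongest reply is that section 4.3 already separates the questions. The factor-time model is introduced for short- and medium-term effects, so the long-term test would be the basic model's interaction, run once at 0.05. On that reading nothing is lost to correction and no error is added. This reading is tenable. A reader might infer from the two sections that power must be 66% or less, or else the error rate must exceed 5%. The documents do not support that either/or.

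Other strong inferences also fail:

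- That the t3 contrast is definitely corrected. The correction sentence speaks of differences between time points, and the group contrasts come in the following sentence.
- That 66% is an upper bound. It needs Bonferroni, a family of exactly three and t3 as the deciding test. Holm gives more.
- That power is 0.48. This needs Bonferroni over all eleven listed contrasts (3 + 2 × 4), a family the protocol never defines.
- That the error rate is nearly 10%. That is the limit for two independent tests (1 − 0.95² = 0.0975), but the slope and the contrasts share the same data. Nor does the protocol say that either may count.

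It is also fair that a condensed article may leave the correction method and family to the analysis plan, and that t-test figures only approximate a mixed model with possible covariates.

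What does not stand is that the slope reading settles the matter. No sentence adopts it, t3 is itself listed among the factor-time contrasts, and step 3 shows that 0.80 is not secured for the slope. Nor is this only omitted detail: the article itself states the alpha, the powered effect, the contrasts, the correction and the exemption, and they do not fit together as written.

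**Conclusion.** The point holds as a mismatch between the powered comparison and the tests listed, with no deciding test named. Its size depends on the reading:

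- t3 contrast, not corrected: the stated 0.80 stands.
- t3 contrast, Bonferroni over three: about 0.66. With Holm and equal effects: about 0.72–0.75.
- Slope at 0.05: from about 0.84–0.85 down to 0.60, depending on whether the effect grows, holds or fades after the 12-week programme.
- Slope or any Bonferroni-corrected between-group contrast: error rate about 8–9%, slightly lower for change contrasts.

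The slope and error-rate figures rest on compound symmetry, and the error rates also on an assumed correlation of 0.5 to 0.9. The protocol's model has random slopes, so the true values will differ. The conclusion that 0.80 is tied to one unnamed test does not depend on those assumptions. This should be corrected before analysis; it does not undermine the design.

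**What to change.** Before analysis, state in section 4.3 or in the analysis plan that, in each trial, the between-group t0–t3 contrast from the factor-time model is the single primary test, at two-sided 0.05. Test t2 and then t1 only afterwards, in fixed order, each only if the preceding test is significant; alternatively, treat them as secondary tests with a named correction. Describe the slope interaction and the within-group contrasts as supportive.

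This matches the comparison that was powered, holds the primary error rate at 5%, and keeps the planned 0.80 with no more participants, provided the assumed d applies to that contrast. Naming the slope instead would also settle which test decides, but the sample size would then need its own justification.

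The cost is one paragraph. The downside is small: under the fixed order, t1 and t2 cannot be claimed as confirmatory if t3 fails, and are then reported with confidence intervals.

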### 2.3. Interventions

#### 2.3.1. Interactive Web-Based Health Program

The intervention group for both clinical trials (F_clin_, W_clin_) will receive the TK-HC. This multimodal health program comprises different coaching modules to enable personalized health coaching according to the chosen health goal and personal health profile. With an evidence-based foundation, it attempts to meet the requirements of quality-assured prevention programs while providing a high degree of usability through interactive, self-directed, and flexible handling [70]. For the present evaluation of the TK-HC, however, the focus will be on individual coaching modules so that the intervention group of the fitness trial (F_clin_) will receive the “TK-FitnessCoaching” (TK-FC) and the intervention group of the weight loss trial (W_clin_) will get the “TK-WeightLossCoaching” (TK-WC). Both coaching modules are intended to achieve sustainable health effects within a 12-week intervention phase to prevent NCDs in the long term. The TK-FC is specialized in promoting physical activity and physical fitness based on endurance, strength, flexibility, and coordination training. The focus of the TK-WC is to assist users in losing and maintaining weight by following the energy density concept and a balanced, healthy diet.

The TK-HC is structured in the same way for both modules. Before starting the program, the user is guided through a multistep anamnesis to check suitability for the chosen health goal and set up an individually tailored program according to the personal health profile. The TK-WC user selects the preferred weight loss goal (3 or 5 kg). After completing the anamnesis, the user is directed to the program platform, consisting of three main areas. The first area (“My health program”) presents a personal dashboard that forms the central part of the program and accompanies the user in everyday life (Figure 1a,b). Here, the user can view an individual weekly plan of daily activities and an overall 12-week coaching plan based on three phases (phase 1: getting to know and trying out (week 1–3), phase 2: consolidating new behaviors (week 4–6), phase 3: anchoring habits (week 7–12)). The user can flexibly adapt these plans to individual needs by selecting activities from 13 fitness (TK-FC) (Figure 2a) and 12 weight loss (TK-WC) (Figure 2b) activities.

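### Between-group contrasts at t1, t2 and t3 in the factor-time model do not use the measured baseline, which costs precision, most of all for body weight

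*Protocol article*

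**What the plan says.** Section 4.3 (Statistical Methods) of the protocol article sets out two uses of one mixed model.

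- **Continuous time.** Time is coded 0 (baseline) to 3. The intercept equation contains a group effect, γ01, and the slope equation contains the time-by-group term, γ11, defined as the difference in change between the arms.
- **Factor time.** For short- and medium-term effects, time becomes a factor. The between-group test is then: "We will test group differences on time points t1, t2, and t3 as between-group contrast". The same paragraph therefore also produces a t3 contrast.

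Age and gender are given as examples of covariates that may enter. The baseline value of the outcome is not mentioned as a covariate, and no common baseline mean is imposed.

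Section 2.6 (Sample Size) says that the sample sizes "were calculated with regard to the long-term effect (t0–t3) of the respective primary outcome", with d = 0.45 for the fitness trial and d = 0.50 for the weight loss trial, and that "a significance level of 0.05 and a statistical power of 0.80 were assumed". For the weight loss trial, "the required case number was *n* = 64 for both study groups". No SD is given, and the section does not say whether d is standardised on the SD of the outcome at a visit or on the SD of change.

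**The concern.** Adults differ in body weight far more than their own weight changes over 15 months. A contrast between arms at one visit that takes no account of starting weight carries all of that between-person spread in its standard error. Section 2.2 limits BMI to 27.5–34.9 kg/m² in the weight loss trial, but height still varies, so the spread in kilograms stays wide.

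Two things are at stake. A real effect on weight at t1 or t2 could be reported as no group difference although the data could show it. There may also be a mismatch within the plan: the sample size is framed on t0–t3, which suggests change, while the visit contrasts are on the scale of weight itself.

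**Working it through.** **1. The plan's own figure.** A two-sided two-sample t-test at 0.05 (noncentral t) with d = 0.50 and 64 per arm has power 0.801. With d = 0.45 and 79 per arm it has 0.803. The stated numbers per arm reproduce.

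**2. What the contrast estimates.** With time as a factor, the group difference at visit t is γ01 + γ11,t. Because γ01 is free, the model fits each arm's mean at each visit separately. With complete data the contrast then equals the difference in raw means. A simulated complete data set (64 per arm, assumed SD 12 kg, r = 0.95, true effect 2 kg) confirmed this:

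| Visit | Model contrast (kg) | Raw mean difference (kg) |
|---|---|---|
| t1 | −1.545 | −1.545 |
| t2 | −0.933 | −0.933 |
| t3 | −1.203 | −1.203 |

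The standard error of the contrast was 1.95 kg. It was 0.67 kg for the time-by-group contrast (difference in change) and 0.66 kg with a common baseline mean. The variance ratio is about (1.95/0.66)² ≈ 9.

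**3. Power on the kilogram scale.** The documents give neither the weight SD nor the baseline–follow-up correlation r, so both are assumed. The standardised difference is Δ/SD for the raw contrast and Δ/(SD·√(1 − r²)) for the adjusted one. With 64 per arm and SD 12 kg:

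| Δ | Raw | Adjusted, r = 0.85 | r = 0.90 | r = 0.95 |
|---|---|---|---|---|
| 3 kg | 0.29 | 0.76 | 0.90 | 0.99 |
| 2 kg | 0.15 | 0.43 | 0.57 | 0.85 |

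Worked case, Δ = 3 kg and r = 0.90: the raw effect is 3/12 = 0.25. The residual SD is 12·√(1 − 0.81) = 5.23 kg, so the adjusted effect is 3/5.23 = 0.574. At a smaller SD of 10.7 kg, raw power for 3 kg is 0.35. Across SD 10–14 kg it runs from 0.39 down to 0.23.

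**4. Power if d = 0.50 is on the SD of change.** Assuming equal SDs at t0 and follow-up, the SD of change is SD·√(2(1 − r)). Then d_raw = 0.50·√(2(1 − r)) and d_adj = d_raw/√(1 − r²). With 64 per arm:

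| r | d_raw | Raw power | d_adj | Adjusted power |
|---|---|---|---|---|
| 0.80 | 0.316 | 0.43 | 0.527 | 0.84 |
| 0.85 | 0.274 | 0.34 | 0.520 | 0.83 |
| 0.90 | 0.224 | 0.24 | 0.513 | 0.82 |
| 0.95 | 0.158 | 0.14 | 0.506 | 0.81 |

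**5. Power if d = 0.50 is on the SD at a visit.** The raw contrast keeps its 0.80, and adjustment lifts power above 0.99 for r of 0.80 or more.

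**6. VO2max (79 per arm, d = 0.45).** On the SD of change, the raw contrast has power 0.80, 0.59 and 0.43 at r = 0.50, 0.70 and 0.80, against 0.90, 0.86 and 0.84 adjusted. On the SD at a visit, the planned 0.80 stands and adjustment raises it to 0.90–0.98 at r = 0.5–0.7.

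All figures are before any correction for multiple testing.

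**The case against.** The strongest reply is that the plan already has a between-group test that uses baseline. This stands. The interaction γ11 is defined as the difference in change and includes t0. In the simulated setting of step 2, the slope test had power 0.80 for a 2 kg effect present from t1. A reader might infer that the whole between-group analysis discards baseline; the article does not support that. It does assign the short- and medium-term questions to the factor-time model, and there the only between-group test it names is the visit contrast.

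A reader might also infer that the trial is powered for an implausible difference. On an assumed weight SD of 10–14 kg, d = 0.50 would mean 5–7 kg between arms, at or above the 3 or 5 kg goals offered to users. That follows only if d is on the SD at a visit. Section 2.6 does not say so, and its t0–t3 wording points to change. The 3 or 5 kg is moreover a user's personal goal within one arm, not a design difference between arms.

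Nor is this bias. Under randomisation the raw contrast is unbiased and keeps its type I error. Chance imbalance in starting weight (one standard error is 12·√(2/64) = 2.1 kg at SD 12 kg) is already counted in its standard error.

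Finally, the covariate list is only illustrative, and multiple imputation may borrow from baseline when data are missing. Both make the identity in step 2 approximate in practice. Neither changes the stated contrast, which targets unadjusted means. The article writes out the equations and names the contrasts, so this is a stated method rather than detail left to a later document.

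**Conclusion.** The point holds for the factor-time contrasts at t1, t2 and t3, and not for γ11. Those contrasts are valid but inefficient, and the loss is largest for body weight. At SD 12 kg and 64 per arm, a 3 kg difference has power 0.29 unadjusted against 0.76–0.99 adjusted for r of 0.85–0.95. These sizes rest on an assumed SD and correlation; the structural result in step 2 does not.

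Whether the visit contrasts fall short of the planned 0.80 depends on the scale of d, which is not stated. On the change scale, their power for body weight is 0.43 to 0.14 as r goes from 0.80 to 0.95. On the visit scale the 0.80 stands, and adjustment only adds power. The sample size calculation itself is not in error. For VO2max the gain depends on r and is smaller if, as seems likely, r is lower than for weight.

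This is a free improvement, not a flaw that invalidates the analysis.

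**What to change.** In section 4.3, change the factor-time model in one of two ways:

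- constrain both arms to a common mean at t0, by dropping the group effect at t0 and keeping the group effects at t1, t2 and t3; or
- model t1–t3 as outcomes, with the t0 value as a covariate.

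Then report the t1, t2 and t3 between-group contrasts as baseline-adjusted differences, for the primary outcome and for every secondary outcome measured at t0. In section 2.6, state whether d refers to the SD at a visit, the SD of change or the baseline-adjusted SD.

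The cost is a change of wording. Table 1 already schedules every primary and secondary outcome at t0, so no extra data or participants are needed.
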